**Unit Proposing:**

HepatoMetabolic Disease Unit - Bambino Gesù Children’s Hospital, IRCCS, Rome

[name]

**Nome of drug:** KRILLING D

**DRUG CLASS MEMBERSHIP:** Dietary food for special medical purposes

**PHARMACEUTICAL FORM:** pearls

**MEDICATION AND 'MARKETING?** YES

**IF YOU ARE INDICATING:** administration of an additional quota of omega 3 fatty acids and vitamin D to the daily diet.

**EXPERIMENTAL PHASE OF RESEARCH:** III

**INDICATIONS FOR USE OF THE DRUG:** Aim of the research will be to evaluate the efficacy and safety of treatment with DHA and vitamin D in children with non-alcoholic steatohepatitis:

- Evaluation of the tolerability of the administration of DHA and vitamin D

- Assessing the effectiveness of the mixture of DHA + Vitamin D in improving the condition score

- Evaluating the effectiveness of DHA and vitamin D in improving haematochemical 'markers' of the evolution of the metabolic syndrome

**INTRODUCTION TO TRIAL**

The non-alcoholic fatty liver disease (NAFLD) Paediatric has in recent years reached epidemic proportions. currently NAFLD affects 3-10% of normal-weight children and 70-80% of those who are overweight / obese. Over the next 10-20 years, many countries WILL doubling the frequency of the disease, making it emergency identify effective therapeutic strategies. the NASH is characterized by hepatomegaly and / or elevated aminotransferase levels and hepatic steatosis in the absence of other known causes of liver disease and / or consumption of alcohol. Histologically is characterized by inflammation and necrosis of the liver tissue. The main risk factor for the development of NASH is obesity. The pathogenesis is still not well known, several studies suggest that oxidative stress is implicated in the pathophysiology of NASH.

The recruited patients receive two capsules a day containing) docosahexaenoic acid (DHA); ii) Vitamin D3, or placebo for 24 weeks. there is provided a follow-up laboratory-instrumental at baseline (screening visit) and every 6 months up to 12 months (52 weeks).

From a clinical point of view the expected result, eliminated hepatocyte oxidative stress caused by inflammation and fibrosis, will be to interrupt the evolution of the disease to cirrhosis and organ failure.

The therapeutic options currently available for the treatment of pediatric patients with NASH are represented by diet and the increase daily physical activity.

The drugs that will be used in this study have the following characteristics:

- DHA is an essential polyunsaturated fatty acid that belongs to the very long chain Omega 3 series, of which the fish fats, derived from alpha-linoleic precursor are rich. As a precursor of eicosanoids, DHA has an anti-inflammatory enzyme effect, which modulate the metabolism of lipoproteins. For these characteristics it has been suggested activity in the prevention of metabolic syndrome.

- VITAMIN D is a fat soluble vitamin produced in the skin from 7-dehydrocholesterol upon exposure to sun light and metabolized in the liver to its active form (1α-25-dihydroxy-vitamin D3). Recent evidence suggests that low levels of vitamin D3 are associated with the onset of NAFLD and its severity, independently of other confounding factors. Although the molecular mechanism underlying this association is not yet fully known, it has been shown that the active form of vitamin D (1α-25-dihydroxy-vitamin D3) modulates the pathway of the response to insulin, suppress the proliferation of fibroblasts and the production of collagen and inflammatory pathways.

**AIM OF THE RESEARCH**

The evidence available thus provide the rationale for the use of DHA and Vitamin D in children suffering from non-alcoholic steatohepatitis, the aim of reducing the oxidative stress in load of hepatocytes and slow the progression of the fibrotic process to load of the liver parenchyma. It is therefore proposed to recruit patients aged between 4 and 16 years, with non-alcoholic steatohepatitis (NASH, documented histologically), with good liver function, to a randomized double-blind study providing for the administration of a mixture containing DHA and vitamin D vs. a placebo for a period of about 6 months (24 weeks).

**PLAN OF RESEARCH AND DETAILED DESCRIPTION OF THE OBJECTIVES AND OF CLINICAL GENERAL AIM:**

**Study Design:** This is a randomized, prospective single-center study, versus placebo in double-blind that can be classified as a Phase III study.

**Research objectives**

Efficacy and tolerability of treatment with DHA and vitamin D in children with nonalcoholic steatohepatitis:

- Evaluating the effectiveness of DHA + Vitamin D in improving 'NAFLD Activity Score' (NAS) of the disease

- Evaluation of the tolerability of the administration of DHA and vitamin D

- Evaluating the effectiveness of DHA and vitamin D in improving haematochemical values 'marker' of the evolution of the metabolic syndrome

**Primary endpoint:** the reduction of the score of the disease in the experimental group compared to the control group.

**POPULATION STUDY:**

**total population:** 66 (33 per randomization arm)

**Their characteristics:** paediatric patients suffering from non-alcoholic steatohepatitis

**healthy volunteers:** no

**Hospitalized patients:** no (admitted to outpatient care)

**outpatients:** yes

**Minor:** yes

**Gender:** Both

**Age:** 4-16 years

**THE STUDY AND 'POLYCENTRIC?** NO

**Inclusion Criteria:**

Biopsy consistent with the diagnosis of NAFLD/NASH

Reduced serum levels of vitamin D aminotransferases (ALT) levels <10 upper limit of normal

hyperechogenicity at liver ultrasound examination suggestive of fatty liver

International normalized ratio (INR) < 1,3 Albumin > 3 g/dl total bilirubin < 2,5 mg/dl

No previous gastrointestinal bleeding

No previous portosystemic encephalopathy

Normal renal function

No hepatitis B, hepatitis C infection

Normal cell blood count

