**PRODUCT:**

Number of investigational products: 1

Proposed ICD code: 571.8

proposed indication**:** TREATMENT OF PATIENTS IN ETA 'PEDIATRIC AFFECTED BY NONALCOHOLIC STEATOHEPATITIS.

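### The inclusion list accepts any biopsy consistent with NAFLD/NASH, while the aim, objectives, population and indication are NASH only, so the children analysed need not match the population claimed

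*Protocol*

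**What the plan says.** Several places in the protocol describe the disease under study, and all but one say steatohepatitis.

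- Aim of the research: children aged 4 to 16 "with non-alcoholic steatohepatitis (NASH, documented histologically").
- Research objectives: "Efficacy and tolerability of treatment with DHA and vitamin D in children with nonalcoholic steatohepatitis".
- Population study: "paediatric patients suffering from non-alcoholic steatohepatitis".
- Product, proposed indication: "TREATMENT OF PATIENTS IN ETA 'PEDIATRIC AFFECTED BY NONALCOHOLIC STEATOHEPATITIS".
- The opening product summary, under indications for use, gives the same target disease.

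The exception is the list against which a child is screened. Its histological item under Inclusion Criteria reads "Biopsy consistent with the diagnosis of NAFLD/NASH".

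The Introduction describes NAFLD as the broad disease, present in 70-80% of overweight or obese children, and says of NASH: "Histologically is characterized by inflammation and necrosis of the liver tissue". The section on data analysis specifies intention to treat, with each patient kept in the arm assigned at randomisation.

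**The concern.** A child whose biopsy shows steatosis without inflammation or necrosis meets the inclusion list but not the condition in the aim. An investigator screening that child gets opposite answers from two sections of one protocol. If the child is randomised, intention to treat keeps the child in the primary comparison.

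What is at stake is the claim. If the list is applied as written, the result may be an average over NASH and fatty liver without NASH, yet it would be offered for a NASH indication. The assumed response rates of 10% and 45% would then also apply to a mixture for which the protocol does not justify them. A statistical analysis plan cannot repair this, because it does not decide who is randomised.

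**Working it through.** **1. Does any other criterion close the gap?**

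| Criterion | Removes fatty liver without steatohepatitis? |
|---|---|
| Biopsy item | No, it names NAFLD as well as NASH and sets no minimum NAS |
| Liver ultrasound | No, it asks only for signs of fatty liver |
| ALT | No, there is a ceiling (10 times the upper limit) but no floor |
| Vitamin D, INR, albumin, bilirubin, renal function, blood count, viral hepatitis, no previous bleeding or encephalopathy | No, none bears on steatohepatitis |
| Exclusions: other liver disease, alcohol, steatosis-inducing drugs, interfering illness | No, they remove other causes of liver disease and interfering factors |

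The wider wording is therefore not narrowed anywhere in the eligibility lists.

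**2. The plan's own power figure.** Inputs from the sample-size section: Fisher's exact test, alpha 0.05, 10% v 45% (the 45% is taken from the prose), 30 evaluable per arm. Sidedness is not stated. Power is the sum, over all pairs (i, j) for which Fisher's test gives p ≤ 0.05, of Bin(i; 30, p_C) × Bin(j; 30, p_E).

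The two-sided result is 0.830, which reproduces the stated 83%; one-sided it would be 0.898. The sample-size arithmetic is not at fault.

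**3. What mixed entry could do to the planned test.** The protocol gives neither the share f of children without NASH nor their response rates, so both are assumed. If NASH children respond at 10% v 45% and the others at rate q, the rate in each arm is

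p = (1 − f) × p_NASH + f × q.

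Three cases, with 30 per arm, two-sided:

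- A: the others respond as NASH children do, so the rates stay at 10% v 45% for any f.
- B: they never respond (q = 0). For f = 10%, 0.9 × 10% = 9% and 0.9 × 45% = 40.5%.
- C: they count as responders in both arms (q = 1), for instance because their NAS is already low at entry and stays low. For f = 10%, 9% + 10% = 19% and 40.5% + 10% = 50.5%.

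| f | A: power | B: rates | B: power | C: rates | C: power |
|---|---|---|---|---|---|
| 10% | 83% | 9% v 40.5% | 76% | 19% v 50.5% | 65% |
| 20% | 83% | 8% v 36% | 68% | 28% v 56% | 50% |
| 30% | 83% | 7% v 31.5% | 58% | 37% v 61.5% | 38% |
| 40% | 83% | 6% v 27% | 46% | 46% v 67% | 28% |

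In B and C the difference shrinks to (1 − f) × 35 points: 31.5, 28, 24.5 and 21. Power falls further in C because the rates lie nearer 50%, where binomial variance is largest.

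**The case against.** The best reply is that the inclusion list was never meant to stand alone. It has no age limit; 4 to 16 years appears only in the aim and the population section. Those sections must therefore also govern entry, and the sentence in the aim that sets the age also requires histological NASH. Read together, a child with simple fatty liver would not qualify. The slash may also be loose shorthand: the Introduction moves from NAFLD to NASH without a clear line, and its first description of NASH would fit fatty liver disease in general. Part of the rationale is broad too, since low vitamin D is linked to the onset and severity of NAFLD and the objective uses the NAFLD Activity Score.

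This shows that the intent is ambiguous, and that much stands. It does not remove the conflict, because the item labelled as an inclusion criterion still names a wider disease than the aim.

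The objection does limit the consequences. A reader might infer that children without NASH will be enrolled, or that the trial cannot answer its question about NASH. The documents do not support either: they permit such entry but do not say that it will happen or how often.

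A reader might also restrict attention to NASH children. At shares of 10, 20, 30 and 40%, 27, 24, 21 and 18 per arm remain, with power of 77, 73, 65 and 55%. Those figures reproduce, but they describe a NASH-only subgroup test that the protocol does not plan. They are not the power loss of the planned comparison.

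**Conclusion.** The inconsistency is real and should be corrected. The aim, objectives, population and indication are NASH only; the histological entry criterion is NAFLD/NASH; nothing else in the eligibility lists excludes fatty liver without steatohepatitis. The randomised and analysed population need not match the claimed one. The stronger statement, that it does not match, goes beyond the documents.

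This conclusion rests on the wording alone. The effect on power is unknown: none in case A, to 46% in case B and 28% in case C at a 40% share. The three cases are illustrations on assumed shares and response rates, not bounds or forecasts.

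**What to change.** Make the inclusion list and the sections on indications for use, aim, objectives, population and proposed indication describe one disease. The sponsor has two ways to do so.

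1. Align the biopsy criterion with the condition already stated in the aim. The cost is an edit and perhaps somewhat slower recruitment. The protocol should also say how NASH is read on the qualifying biopsy and when that biopsy is taken, since it gives no histological threshold and the screening visit lists no biopsy. The 10% v 45% assumption can stay as stated.
2. If NAFLD without NASH is meant to be eligible, restate the aim, objectives, population and indication as NAFLD including NASH, and limit the conclusion to that population. The cost is a broader, less specific claim. This is more than rewording: the 10% v 45% response rates must be re-justified for the mixed population and the sample size checked against them.

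Neither route adds a procedure, because the inclusion list already requires a biopsy.

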**Exclusion Criteria:**

Alcohol consumption

Use of drugs known to induce steatosis or to affect body weight and carbohydrate metabolism

Autoimmune liver disease, metabolic liver disease, Wilson's disease, and a-1-antitrypsin-associated liver disease

Every clinical or psychiatric disease interfering with experimentation according to investigator's evaluation

Finding of active liver disease due to other causes

**CRITERIA FOR THE INTERRUPTION OF TREATMENT:**

Adverse events

All adverse events which occurred during the course of the clinical study will be reported in the case report form that will be completed for each individual patient. An adverse event is defined as any adverse change with respect to the patient's pre-treatment basal conditions regardless of whether the event is or is not considered treatment-related. This includes all relevant laboratory abnormalities and new illnesses that occur or worsen during the treatment period. It is considered treating any medication administered during the study. The intensity of adverse events will be evaluated using a 3-point scale (mild, moderate, severe). It must also be always documented the relationship between the adverse event and the treatment in progress.

| Severity of adverse events | |
| --- | --- |
|  | |
| Mild | You notice a malaise, but do not have any impairment of normal daily activities |
| Moderate | Malaise enough to reduce or affect normal daily activities |
| Severe | Incapacitating with inability to work or perform normal daily activities |
| Life-threatening | It represents an immediate threat to the patient's life |

Any adverse reactions will also be classified according to the "grading" NCI / NIH (see Annex). In case of serious adverse events, the Ethics Committee will be warned.

Laboratory tests on the safety of the treatment:

- The toxicity data be evaluated based on the exams required by the study design.

The treatment will be suspended the following conditions:

- Toxicity of grade III-IV according to the NCI / NIH criteria;

- If the patient expressing the intention to stop treatment

The expected period of the Experiment: 12 months in total including six months for enrollment and 24 weeks in patient enrolled.

SCHEDULED DATE FOR START OF EXPERIMENTS: October 2013

**TYPE OF STUDY AND EXPERIMENTAL DESIGN AND ITS DESCRIPTION:**

Study: prospective, randomized, Phase III, placebo, with double blindness.

The patients will be randomized into two groups to receive oral emulsion of docosahexaenoic acid (DHA) + Vitamin D3 for oral use pearls (the experimental group), or placebo (control group) that will be made of an inert substance ( corn oil) of that aspect of the pearls of DHA and vitamin D, and will be provided with the product KRILLING D from Italchimici. The requirements concerning the arrangements for daily administration and conservation of the drug will be provided by the Unit of Hepatometabolic Diseases of our Hospital to parents at enrolment.

The assessment of candidates to the inclusion in the protocol in question will be carried out by the Medical of Unit of Hepatometabolic Diseases.

The formulation of the suitability will be based on clinical assessment and the instrumental and laboratory investigations performed. At enrolment in the protocol, we will ask the parents to sign the attached consent form informed the study.

The expected duration of treatment is 24 weeks (approximately 6 months). All patients (and those randomized to the pearl of DHA and vitamin D, both those in the control arm) will be followed every 6 months at our Hepatometabolic Diseases and will undergo check-up, serological and instrumental exams. At the time of study and each semester it will be collected a blood sample for serum bank.

If any patient’s toxicity will not be logged continue the treatment until the end of the period. In case of onset of toxicity or some serious adverse event in some patients, the study will be immediately suspended. Should patients experience an increase in transaminases (equal to or> 6 x N), will be subjected to a clinical and laboratory control with monthly dosing of liver function tests (GOT, GPT, total and fractionated bilirubin, alkaline phosphatase, gamma GT, proteinaemia total, albumin, Quick time and immunoelectrophoresis protein).

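### The protocol holds two conflicting safety-suspension rules: one stops treatment at grade III-IV toxicity, the other stops the study on ungraded toxicity or a serious event

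*Protocol*

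**What the plan says.** Only the protocol is at hand. Two of its sections deal with stopping for safety.

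**Criteria for the interruption of treatment.** The list opens with "The treatment will be suspended the following conditions" and has two entries: "Toxicity of grade III-IV according to the NCI / NIH criteria" and "If the patient expressing the intention to stop treatment". A serious adverse event is not on the list. It is covered earlier in the section: "In case of serious adverse events, the Ethics Committee will be warned". Adverse events are defined "regardless of whether the event is or is not considered treatment-related", although the relationship to treatment must be documented. The section also says that toxicity is to be judged from the examinations that the study design calls for.

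**Type of study and experimental design.** A patient without recorded toxicity continues treatment to the end of the period. Then comes: "In case of onset of toxicity or some serious adverse event in some patients, the study will be immediately suspended". The next sentence begins "Should patients experience an increase in transaminases (equal to or> 6 x N" and prescribes monthly clinical and laboratory checks, with no suspension.

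Two other places bear on these rules. The inclusion criteria admit children with "aminotransferases (ALT) levels <10 upper limit of normal". The visit list, in the section on data management and evaluation, has laboratory work at screening (T0), after 6 months of treatment (T1) and at 12 months. Treatment lasts 24 weeks.

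**The concern.** Stopping rules are applied by clinical staff, often under time pressure, and they work from the protocol. Here the same event can call for two different actions, so staff who follow one section may depart from the other. The study-level sentence is also open-ended. It does not say how many children must be affected, how severe a toxicity must be, whether a serious event must be related to the product, who decides, or how the study resumes.

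Two things are at stake. One is the safety of children aged 4 to 16, which depends on a rule that can be followed without guessing. The other is completion: a literal application could suspend a 66-child trial for a low-grade toxicity or for an event unrelated to the product. Because toxicity data are collected without knowledge of the arm, that event could just as well occur on placebo.

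**Working it through.** **Step 1: the two rules side by side.**

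| Question | Interruption criteria | Type of study and design |
| --- | --- | --- |
| What is suspended? | Treatment | The study |
| Which toxicity? | Grade III-IV | Any onset, no grade given |
| What follows a serious adverse event? | Notice to the Ethics Committee; not among the suspension conditions | Suspension |
| Must the event be related? | Not for an adverse event | Not stated for a serious event |
| How many children? | The individual patient | Plural, no number |
| How does it resume? | Not stated | Not stated |

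**Step 2: two test cases.**

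- A grade I or II toxicity: under the interruption criteria treatment goes on; under the design section suspension follows.
- A serious event unrelated to the product and not a grade III-IV toxicity: under the interruption criteria the Ethics Committee is told and no suspension is listed; under the design section suspension follows.

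Suppose the study in the design section means the affected child's participation. The first row of the table then agrees, but both test cases still come out differently. The contradiction does not depend on how that word is read.

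**Step 3: how often a study-level rule might fire.** The protocol gives no figure on this point to reproduce and no serious-event rate. The one input from the document is N = 66 (33 per arm), under population study. The per-child risk r of at least one serious event from any cause, over the time the rule is in force, is an assumption, shown at 1%, 2% and 5%. Children are taken as independent.

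- One child suffices: P = 1 - (1 - r)^66
- Two children needed: P = 1 - (1 - r)^66 - 66 r (1 - r)^65

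| r (assumed) | (1 - r)^66 | 66 r (1 - r)^65 | One child suffices | Two needed |
| --- | --- | --- | --- | --- |
| 1% | 0.515 | 0.343 | 0.485 (48% from the unrounded 0.4849) | 0.141 (14%) |
| 2% | 0.264 | 0.355 | 0.736 (74%) | 0.381 (38%) |
| 5% | 0.034 | 0.118 | 0.966 (97%) | 0.848 (85%) |

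These cover serious events only. Ungraded toxicity is a further trigger, but the document offers no basis for putting a number on it.

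**Step 4: the connected provisions.**

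- Toxicity is to be judged from the scheduled examinations, yet no laboratory visit is listed between T0 and month 6. With 24 weeks of treatment, the first listed laboratory check after screening falls at about the end of treatment. As scheduled, a trigger that shows only in the laboratory would be found too late to alter treatment.
- The inclusion line on ALT is garbled; read as below 10 times the upper limit of normal, it lets a child enter above 6 x N. The monitoring rule speaks of an increase, and the text does not say whether it covers a child who was above that level from the start.

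**The case against.** The strongest reply is that the English is a rough translation. The sentences on either side of the study-level sentence manage individual patients, so the study may simply mean the affected patient's participation. That is plausible, and it is why the point is not put as a trial-wide rule. It does not remove the conflict, as Step 2 shows, and a safety rule whose unit has to be guessed needs correcting anyway.

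Second, telling the Ethics Committee is compatible with suspending, so the two responses to a serious event need not exclude each other. Both can indeed be done. The discrepancy is that a serious event is missing from the listed suspension conditions in one section and is a ground for suspension in the other.

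Third, toxicity implies an effect of treatment. That stands: the missing causality condition matters for serious events, not for toxicity.

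Fourth, clinical toxicity and serious events can be noticed and recorded without a scheduled blood sample. That also stands, and it confines the visit-list point to laboratory findings.

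A reader might infer that the 6 x N rule contradicts the entry limit. It does not: it concerns an increase and leads only to monitoring. What is left is a question of scope.

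A reader might also infer from the intention-to-treat statement that a child who stops product must have the final biopsy. That statement only fixes the arm in which each child is analysed. Whether such a child has a biopsy is a clinical matter that it does not settle.

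**Conclusion.** The contradiction is real. The two sections differ on the toxicity grade that leads to suspension and on what follows a serious event and, on the literal wording, on whether treatment or the whole study is suspended. The study-level sentence also lacks a number of events, a causality condition for serious events and a restart rule.

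A reader might conclude that one event ends the trial. The document does not say so: it speaks of patients in the plural and of suspension, not termination. A one-event trigger is a possible reading, not the stated rule. Nor does the document support saying that the trial would probably be halted. The range of 14% to 97% in Step 3 comes from assumed risks, independence between children and an unsettled trigger count, and even the one-child reading gives slightly under one half at a 1% risk. The figures show only that the ambiguity could matter at this sample size.

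The weight is moderate. It is an internal inconsistency in a safety rule and should be corrected, but it does not itself touch the randomisation, the sample-size calculation or the planned analysis.

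**What to change.** Reconcile the interruption criteria and the design section into one rule, stated once and cross-referenced. It should say separately what suspends a child's treatment and what suspends the study. For the study level it should make explicit the severity, the number of events, whether relatedness counts, who decides and how the study resumes. All thresholds and clinical choices are for the investigators.

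In the same edit:

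- Reconcile the statement that toxicity is judged from the scheduled examinations with a visit list that has no laboratory visit between T0 and month 6.
- State whether the 6 x N monitoring rule applies to a child who enters above that level.

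The cost is protocol wording; the reconciliation itself needs no new procedure. If the investigators decide to add laboratory visits, that is a separate decision with its own cost.
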